## Abstract

**Introduction:**

Patients undergoing curative gastrectomy for gastric cancer are vulnerable to perioperative protein loss, negative nitrogen balance and delayed recovery. Conventional peripheral parenteral nutrition (PN) formulations may not provide sufficient protein at clinically practical infusion volumes, and whether high-protein (amino acid–enriched) PN improves postoperative nitrogen balance after gastrectomy has not been tested in a randomized controlled trial. The PROGAIN trial evaluates the effect of perioperative high-protein PN on nitrogen balance and recovery outcomes in this population.

**Methods and analysis:**

PROGAIN is a single-center, randomized, open-label, parallel-group superiority trial with blinded laboratory assessment and coded-group analysis of the primary endpoint. The trial will enroll 110 patients with gastric cancer scheduled for curative gastrectomy. Participants are allocated 1:1 to high-protein PN or conventional PN, administered through a peripheral intravenous line on the day before surgery and postoperative day (POD) 1 through POD 5. PN is delivered at a daily caloric target of 20 kcal/kg/day using a stepwise schedule informed by an institutional retrospective audit of oral intake. The primary outcome is nitrogen balance on POD 5, calculated using a simplified Blackburn equation. Secondary outcomes include nutritional indices, skeletal muscle index, glycemic control, postoperative complications classified by Clavien–Dindo grade and functional recovery measures. The primary analysis will compare the two arms using a two-sample t-test in the intention-to-treat population. The trial has 80% power to detect a between-group mean difference of 3 g/day at a two-sided α of 0.05.

**Ethics and dissemination:**

The trial is approved by the Institutional Review Board of Soonchunhyang Cheonan Hospital and conducted in accordance with the Declaration of Helsinki and ICH–Good Clinical Practice. Findings will be disseminated through peer-reviewed publication, scientific meetings and results reporting on ClinicalTrials.gov.

**Trial registration:**

ClinicalTrials.gov, NCT07488611.

## Introduction

Gastric cancer is a leading cause of cancer-related morbidity and mortality worldwide and is highly prevalent in East Asia [1]; in the Republic of Korea, it is the fourth most common cancer [2]. Although gastrectomy is the cornerstone of curative treatment, it substantially alters digestive anatomy and physiology, reduces oral intake and nutrient absorption, and provokes a systemic surgical stress response that contributes to marked perioperative deterioration in nutritional status.

Cancer-related malnutrition affects approximately 41% of patients globally and is associated with a substantially increased risk of mortality and postoperative complications [3]. The early postoperative period after gastrectomy is characterized by an acute catabolic state, peaking within the first 48–72 hours, in which accelerated whole-body protein breakdown produces a markedly negative nitrogen balance and progressive depletion of skeletal muscle mass [4,5]. Inadequate perioperative protein supply is linked to delayed wound healing, infectious complications, prolonged hospital stay, and impaired tolerance of adjuvant chemotherapy [6,7] — consequences particularly relevant in gastric cancer surgery, where postoperative oral intake is restricted and highly variable between patients, yet the actual protein delivery achieved during this period has not been prospectively quantified. Our institutional experience has likewise highlighted the clinical importance of postoperative nutritional status after gastrectomy in patients with gastric cancer [8,9]. These findings position perioperative nutritional state as a modifiable determinant of the gastric cancer treatment trajectory.

To attenuate the catabolic response and support recovery, current European Society for Clinical Nutrition and Metabolism (ESPEN) cancer guidelines recommend a daily protein intake of at least 1.0 g/kg, increasing to 1.5 g/kg or higher in patients with sarcopenia, advanced age, or established malnutrition [7]; the 2025 update to the ESPEN guideline on clinical nutrition in surgery reaffirms perioperative protein supplementation as a central component of recovery-oriented care [10]. Among older adults and critically ill patients, evidence further supports protein delivery up to 2.0 g/kg/day to preserve lean body mass [11,12]. However, conventional peripheral parenteral nutrition (PN) formulations were not designed to meet these targets at clinically practical infusion volumes. High-protein (amino acid–enriched) PN formulations have been developed to deliver more nitrogen at the same daily volume, with a correspondingly lower non-protein calorie-to-nitrogen ratio (Table 2). At the trial’s caloric target, conventional PN provides approximately 0.9 g/kg/day of protein equivalent from amino acids (below the ESPEN minimum of 1.0 g/kg/day), whereas high-protein PN provides approximately 1.1 g/kg/day, thereby bringing protein delivery within the ESPEN-recommended range (1.0–1.5 g/kg/day) while remaining feasible via peripheral venous access [7,10].

Despite this rationale, prospective evidence for the clinical effectiveness of high-protein PN in patients undergoing gastrectomy is lacking. Trials in critically ill patients have demonstrated that high-protein nutritional support improves measures of protein metabolism [12]; observational data after oesophagectomy suggest that protein-enhanced feeds attenuate postoperative catabolism [13]; a randomized study of arginine-enriched early enteral nutrition has shown improvements in nitrogen balance after total gastrectomy [14]; and a systematic review of high-protein home PN has documented favorable effects in oncology patients [15]. Although these studies support the biological plausibility of enhanced protein delivery, their populations, routes of nutrition, and clinical contexts differ substantially from perioperative PN after gastrectomy for gastric cancer. However, no randomized controlled trial has directly compared a high-protein PN formulation with a conventional formulation in adults undergoing curative gastric cancer surgery.

The PROGAIN trial was designed as a randomized, open-label, parallel-group superiority trial to evaluate whether perioperative administration of a high-protein PN formulation improves postoperative nitrogen balance compared with a conventional formulation in patients undergoing curative gastric cancer surgery. Nitrogen balance on postoperative day (POD) 5 was selected as the primary endpoint because it is an objective, quantifiable physiological marker of net protein metabolism that can be measured directly from 24-hour urinary urea nitrogen and dietary protein intake, has been used to evaluate perioperative protein supplementation in upper gastrointestinal cancer surgery [13,14,16], and is sensitive to short-term changes in protein delivery on a clinically relevant timescale. Although nitrogen balance has been used as a primary or principal endpoint in perioperative and nutritional randomized trials [17,18], an improvement is not guaranteed by increased protein delivery: in the catabolic state after major surgery, additional amino acids are frequently oxidized rather than retained, and several randomized trials of enriched amino-acid regimens have found no improvement in nitrogen balance [16,18]; the trial therefore tests whether this formulation produces genuine net nitrogen retention. We hypothesize that perioperative high-protein PN will improve nitrogen balance on POD 5, with secondary benefits on nutritional, glycemic, and functional recovery outcomes. The trial is registered at ClinicalTrials.gov (NCT07488611).

## Methods and analysis

### Study design and setting

PROGAIN is a single-center, prospective, parallel-group, two-arm, randomized, open-label superiority trial comparing high-protein PN with conventional PN in adults undergoing curative gastric cancer surgery, with 1:1 allocation between the investigational and control arms. The trial is conducted at the Department of Surgery, Soonchunhyang University Cheonan Hospital, Korea. The protocol is reported in accordance with the Standard Protocol Items: Recommendations for Interventional Trials (SPIRIT) 2025 statement [19] (the completed SPIRIT 2025 checklist is provided as S1 Checklist), and the trial will be reported at completion in accordance with the Consolidated Standards of Reporting Trials (CONSORT) 2025 statement [20]. The trial is registered at ClinicalTrials.gov (identifier NCT07488611).

### Eligibility criteria

Adults aged 19 years or older who are scheduled to undergo curative gastric cancer surgery and provide written informed consent are eligible. Detailed inclusion, exclusion and withdrawal criteria are presented in Table 1. Eligibility is based on the planned extent of resection: planned total and distal (subtotal) gastrectomy are eligible, whereas planned proximal gastrectomy is excluded; all standard reconstructions (Billroth I, Billroth II, Roux-en-Y) and surgical approaches (open, laparoscopic, robotic) are permitted. If the actual procedure differs from the plan (including an unplanned proximal gastrectomy), the participant is retained and analyzed in the allocated arm under the intention-to-treat principle, with the actual procedure recorded and examined in per-protocol and sensitivity analyses. Patients with clinically significant hepatic or renal impairment are excluded by the screening laboratory thresholds listed in Table 1, and hepatic and renal function are monitored daily during the intervention.

**Table 1 pone.0355677.t001:** Inclusion and exclusion criteria.

Inclusion criteria	Exclusion criteria
1. Adults ≥19 years of age scheduled to undergo curative gastric cancer surgery	1. Uncontrolled severe comorbidity, including: • Decompensated diabetes mellitus • Cerebrovascular or major cardiovascular event (acute myocardial infarction, stroke, pulmonary embolism) within the prior 6 months • Sepsis • Heart failure
2. Able and willing to provide written informed consent	2. Receipt of parenteral nutrition within 7 days prior to randomisation
	3. Severe preoperative metabolic abnormality on screening laboratory tests, defined as any of: • Triglyceride > 400 mg/dL • AST or ALT > 3 × upper limit of normal (ULN) • Total bilirubin > 3 × ULN • Serum creatinine > 2 × ULN • HbA1c > 9.0% • Potassium < 3.0 or > 6.0 mEq/L • Calcium > 12.5 mg/dL • Sodium > 155 mmol/L • Magnesium > 3.0 mg/dL
	4. Any other condition that, in the investigator’s judgment, makes the participant unsuitable for the trial 5. Planned proximal gastrectomy

Withdrawal criteria: participants who develop severe intra- or postoperative complications (e.g., massive hemorrhage requiring re-operation) or severe infusion-related events that preclude further peripheral parenteral nutrition (e.g., refractory infusion-site pain or phlebitis) will be withdrawn from the per-protocol analysis but retained in the intention-to-treat population.

### Recruitment

Potential participants are identified during preoperative outpatient consultations among patients scheduled for curative gastric cancer surgery. The enrolling investigator screens eligibility against the inclusion and exclusion criteria during the preoperative evaluation, provides verbal and written information about the trial — including its objectives, procedures, potential risks and benefits, and the participant’s right to withdraw at any time without consequence to standard of care — and obtains written informed consent before any trial-specific procedure is undertaken.

### Randomization and allocation concealment

**Random sequence generation.** Eligible participants are randomly allocated in a 1:1 ratio. The master allocation sequence was generated in advance for 120 sequential allocations using a custom Python script, with a fixed seed and permuted blocks of variable size (4 and 6) in randomly chosen order. Stratified randomization is not used because the anticipated low proportion of total gastrectomy would produce imbalanced strata and incomplete blocks in the small stratum; extent of gastric resection and baseline nutritional status are instead controlled analytically through a prespecified covariate-adjusted (ANCOVA) analysis, and a subgroup analysis by extent of resection (total versus distal gastrectomy) is prespecified as exploratory in the Statistical analysis section.

**Allocation concealment.** The master sequence is held in read-only form by a single dedicated clinical research coordinator (CRC) in a password-protected directory inaccessible to any other member of the trial team. The CRC has no role in determining participant eligibility, enrolling or consenting participants, administering the assigned interventions, or assessing study outcomes, ensuring that knowledge of the allocation sequence cannot influence enrollment decisions or outcome assessment. File integrity is verified by a SHA-256 cryptographic checksum computed at the time of sequence generation and stored separately, providing an audit trail against post-hoc modification; allocation concealment per se is ensured by the procedural safeguards described in the Allocation procedure section.

**Allocation procedure.** Once eligibility is confirmed and written informed consent obtained, the enrolling investigator notifies the CRC of the participant’s study identifier (PROGAIN-NNN, assigned in enrollment order). At each randomization request, the CRC opens the master sequence file in read-only mode, identifies and communicates only the next sequential assignment to the investigator, and does not preview upcoming allocations. The allocation is therefore disclosed to the enrolling investigator only after the participant’s eligibility has been confirmed and written informed consent obtained. The assignment is recorded immediately in a dedicated randomization log capturing study identifier, sequence number, group, date and time of allocation, allocator’s identifier, method, seed, and notes; the log is exported as a system-timestamped, non-editable PDF for archival after allocation updates or at predefined monitoring points*.*

**Blinding.** Because the products differ in labeling, blinding of participants, bedside investigators, and the ward nursing and nutrition support (NST) is not feasible; the trial is open-label for these parties. To minimize outcome-assessment bias, laboratory measurements (including the primary 24-hour urinary urea nitrogen assay), computed tomography–based skeletal muscle indices, and Clavien–Dindo classification of postoperative complications are performed without knowledge of group allocation. For the primary endpoint analysis, the dataset is prepared with intervention assignments replaced by coded group labels (Arm A/ Arm B), and daily amino-acid intake is recorded in grams without product identifiers. The analyst remains blinded to coded arm identity until the primary analysis is locked. Daily oral intake is recorded as a patient-reported outcome: after standardized in-hospital education, participants complete a meal-by-meal intake form that is verified by the nutrition support team; because this self-reported intake enters the numerator of the primary endpoint, it is a potential source of ascertainment bias in this open-label trial, which was one reason for selecting an objective, blinded assay (urinary urea nitrogen) for the primary endpoint. Postoperative complications are graded by an assessor blinded to allocation using the Clavien–Dindo classification, and standardized institutional discharge and diet-advancement criteria are applied. The coded group labels (Arm A/ Arm B) are unmasked by an independent individual only after database lock and finalization of the statistical analysis plan.

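### The running randomization log records the fixed seed, so a key input for rebuilding the allocation list lies outside the only access restriction the protocol states

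*Protocol article*

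**What the plan says.** All of the relevant text is in the protocol article, under Randomization and allocation concealment.

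- **Random sequence generation.** A list of 120 assignments was made beforehand by a Python program written for the trial, "with a fixed seed and permuted blocks of variable size (4 and 6) in randomly chosen order".
- **Allocation concealment.** The master sequence is read-only and held by one coordinator "in a password-protected directory inaccessible to any other member of the trial team". That coordinator has no part in eligibility, consent, enrollment, treatment or outcome assessment. A SHA-256 checksum guards the file against later alteration. The paragraph then says that "allocation concealment per se is ensured by the procedural safeguards described in the Allocation procedure section".
- **Allocation procedure.** The coordinator discloses one assignment at a time, after eligibility and consent. Each assignment goes into a log that shows, among other things, its place in the sequence and the arm. The end of the list of fields and the start of the export rule read: "identifier, method, seed, and notes; the log is exported as a system-timestamped, non-editable PDF for archival after allocation updates". Export may also happen at set times for monitoring.

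Under Blinding, participants, bedside investigators, ward nurses and the nutrition support team know the treatment given. Under Trial status, recruitment is expected to run to February 2027.

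**The concern.** The protocol protects the list as a file, but the list is also the output of a program. Whoever has the program and its seed has the list without opening the file. The procedure copies the seed into a running record that is exported repeatedly while patients are still being enrolled, and the stated access restriction covers only the master sequence. The seed field also sits in the section on which concealment is said to rest.

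The purpose at stake is the usual one: whoever decides on enrollment must not be able to foresee the next arm. Here the enrolling investigator screens, takes consent and learns each allocation, and Table 1 includes an exclusion that rests on the investigator's judgment. If upcoming assignments were known, the choice or order of patients could follow them. The primary two-sample t-test would have no protection against that. The planned ANCOVA adjusts for extent of resection and baseline nutritional status, so it would deal with selection on those factors only.

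**Working it through.** The plan gives no figure for predictability, so there is none to reproduce. The check has three steps.

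**1. What is protected and what is not.**

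| Item | Where it is mentioned | Access restriction stated in the article |
|---|---|---|
| Master sequence (120 places) | Allocation concealment | Yes: the coordinator only, behind a password |
| Generating script | Random sequence generation | None stated |
| Seed | Sequence generation; log field in Allocation procedure | None stated |
| Log and its PDF exports | Allocation procedure | None stated |

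The checksum shows whether the file has been altered. It does nothing to stop the list being generated again from its inputs.

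**2. Does seed plus script give the list?** An illustrative generator of the stated design (blocks of 4 and 6 in random order, 120 places) was run twice with one seed. The two lists agreed in 120 of 120 places. This shows only that seeded code is deterministic, which is all that is needed: with the trial's own script and seed, all 120 assignments follow. The log also holds sequence number and group, so a rebuilt list can be checked against past assignments. The seed without the script does not give the list, because the result depends on the random-number generator and the order in which the code calls it.

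**3. What would the seed add to what is already predictable?** Consider an observer who knows the block sizes, which the article states, and all past assignments.

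- Let p be the probability that the next assignment is the investigational arm, given the past.
- Expected share guessed correctly = mean of max(p, 1 − p) over the list.
- Share known with certainty = proportion of places where p is 0 or 1.
- Assumption: blocks of 4 and 6 are equally likely. The article says the order is random but gives no probabilities.

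Over 4,000 simulated lists of 110:

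- Guessed correctly: 0.691, that is 0.691 × 110 ≈ 76 participants.
- Known with certainty: 0.055, that is 0.055 × 110 ≈ 6 participants.
- With seed and script: 1.00 on both measures.

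For a person holding both, the gain over ordinary guessing is 100 − 69 = 31 percentage points. The 69% comes from the block design and knowledge of past assignments, and owes nothing to the seed.

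**The case against.** The strongest reply is that nothing has been shown to leak. The log reads naturally as the coordinator's own audit record, and its PDFs are for archiving. The coordinator already holds the full list and enrolls no one, so a seed in that person's log exposes nothing new. To predict assignments, someone who influences enrollment would need both the log and the exact script, and the article gives them neither. Who may read the log and where the script is stored are details that a journal article can leave to the full protocol, cited as S1 Protocol and not shown here.

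Most of this stands. A reader might infer that the logged seed defeats the password, or that the seed is as good as the list. The document supports neither reading. A reader might also turn the gain in predictability into a bias in nitrogen balance. That requires an assumed selection effect per forecast, and an assumption that patients already scheduled for cancer surgery are placed according to forecasts. The document supplies neither, so any such figure would reflect the input chosen. Nor does the open-label design create the weakness. A known list harms concealment in any trial, and open treatment mainly helps an observer verify a rebuilt list.

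What the reply does not remove is the stated rule. The article's silence on who reads the log may be due to condensation, but its instruction to record the seed there is explicit. That instruction has little to set against it: a fixed seed is the same on every row, and the checksum with one restricted copy of the seed serves the audit purpose.

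**Conclusion.** The point holds as a conditional and avoidable weakness in allocation concealment, not as a failure of it. An input that, together with the script, determines all 120 assignments is copied into a record for which the article states no access limit, during recruitment, in the section said to secure concealment. For a person holding both seed and script, predictability would be 100%, against about 69% without them (blocks of 4 and 6 equally likely, all past assignments known). Whether any such person exists cannot be told from the document. No bias in the arm difference can be attributed to the seed. The point is minor in standing, but the correction is nearly free and is useful only if made before the remaining allocations.

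**What to change.** 1. Delete the seed from the log fields, and keep it out of the log and its exports until enrollment is complete.
2. Redact the seed from PDFs already exported. Keep the unredacted originals with the master sequence so that the audit trail is not lost.
3. Store the seed and the generating script under the same access restriction as the master sequence, and say so in the protocol. State also who can read the log.
4. Establish whether anyone involved in enrollment has had access to both seed and script. Regenerate the unused part of the list only if so, and only with IRB approval.

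Steps 1 to 3 cost one wording change and some redaction. If the log fields are part of the approved protocol, the change also needs the IRB approval that the Ethics and dissemination section requires before any amendment is implemented. Sample size, endpoints and analysis are unaffected.

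Step 4 should not be taken as a precaution. Regeneration would replace the checksummed list and end the single unchanged allocation method described under Trial status. It could also leave two incomplete blocks, one at the changeover and one when enrollment stops at 110. Each can leave an imbalance of up to 3, so up to 3 + 3 = 6 in total.
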